### Statistical Analysis

The main analysis will be an intent-to-treat analysis. The quantitative outcomes will be estimated with 95% CI. Quantitative variables will be expressed by mean values and standard deviations. The 6-month follow-up period for the 25 participants will allow us to record the number and frequency of alerts generated by the solution. A total of 3 positive predictive value (PPV) calculations (estimation of legitimate alerts) will be done (95% CI, thanks to end users’ feedback for the overall follow-up period and for each 2-month follow-up period: 0-2 months, 2-4 months, and 4-6 months) to estimate the progression of algorithm performance. For the secondary objective, we will also analyze these 3 periods to evaluate the performance of the automatic alerts in detecting changes in functional or cognitive autonomy or major events (sensitivity, specificity, predictive value, and receiver operating characteristic [ROC] curves). Alerts will be addressed with both a binary approach (no alert vs 1 alert to estimate sensibility, specificity, PPV, and negative predictive value) and a continuous approach (number of alerts over the period to plot an ROC graph and estimate the area-under-the-curve). The Department of Epidemiology at our University Hospital will conduct statistical analyses using SAS version 9.4 (SAS Institute, Inc).

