### Study Measures

The primary aim is to assess the sensitivity and specificity of the solution, defined as the ability to trigger alerts deemed relevant by the recipients: older adults, care partners, and professional support workers. To this end, both conventional and automatic alerts will be recorded during the follow-up period. Following each alert, the CRA gathers subjective feedback from the participant (for automatic alerts only), the care partner, and the telecare worker: *Was it relevant to alert you?* The alerts are also described (number, time of the day, duration of the communication if a communication is established, subject of the call in case of a conventional alert, and solutions proposed).

The secondary aim is to evaluate the ability of the system to detect a functional or cognitive decline and any major event. All major medical events, defined as any event resulting in in-home physician or paramedic intervention, or a call to the emergency services, are collected retrospectively by the CRA every 2 months (by phone).

Sociodemographic and health data are collected at baseline. The participants’ cognitive and functional parameters are assessed at baseline and at the end of follow-up: MMSE (ranging from 0 to 30; the greater the score, the greater the global cognition) [15]; ADL (ranging from 0 to 6, the greater the score; the greater the functional autonomy in daily life) [13]; Instrumental activities of daily living (ranging from 0 to 8; the greater the score, the greater the functional autonomy in daily life, eg, ability to use the telephone) [16]; Cardiovascular Health Study frailty index criteria (unintentional weight loss, self-reported exhaustion, weakness, slow walking speed, and low physical activity) [12]; Short Physical Performance Battery (consisting of a balance test, a 3-m walking test, and a 5 chair-rises test; score ranging from 0 to 12 with 12 indicating the highest degree of functioning) [17].

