## Discussion

### Strengths and Limitations of Our Study

Older adults express the desire to live autonomously in their own homes. Clinicians, on the other hand, have difficulty monitoring the functional and cognitive autonomy of seniors over time because of the limitations associated with in-person measurements and self-reported data [5]. To date, despite the rapid pace at which research projects and commercial electronic health devices are developing, few solutions really meet these daily needs. We believe that, following a learning phase, our low-cost unobtrusive solution could trigger alerts if the sensors were to detect an acute, unusual event or a subtle change in everyday habits over time. This solution could provide relevant information to care partners and health professionals to support patient follow-up. The originality of our real-life project lies in the choice of the primary outcome and in our user-centered evaluation rather than in the technical specifications. We will evaluate the relevance of the alerts according to the end users and the progression of our algorithm performance over time. One of the main obstacles to the wide dissemination of alert systems is the low acceptability to end users (eg, false positive alarms) and the difficulty of integrating this approach into a complex and overburdened health care system. In our study, the primary endpoint is determined by the end users themselves. We strive to go beyond traditional medical event considerations such as severe falls, minor falls and minor events, and major events, which do not always make sense for older people. The strengths of our monitoring and support solution can be summarized in several points: it meets the needs of older people living alone; it includes an end user assessment; it is a nonintrusive solution; we use inexpensive sensors without heavy maintenance; and finally, the learning algorithm should increase the solution’s performance over time based on the end user feedback.

Concerning the potential limitations, we plan to analyze the performance of automatic alerts in detecting major events and changes in participants' autonomy (to calculate the number of subjects to be included for a future study). Although our population is at high risk, it is likely that the duration of follow-up is insufficient, particularly for autonomy loss. However, our center implements other studies in comparable populations on which we can rely for such a sample size calculation.

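### The primary analysis judges progression of the algorithm by period PPV only, and PPV can rise while fewer relevant alerts reach users

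*Protocol article*

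**What the plan says.** The Objectives section makes the evolution of algorithm performance over time, as judged by recipients, part of the primary objective. Statistical Analysis names the measure: "A total of 3 positive predictive value (PPV) calculations (estimation of legitimate alerts) will be done", from end-user feedback, for the whole follow-up and for months 0-2, 2-4 and 4-6, "to estimate the progression of algorithm performance". No other measure against user-judged relevance is attached to progression.

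Study Measures describes the rating: "Following each alert, the CRA gathers subjective feedback from the participant" (automatic alerts only), the care partner and the telecare worker, with the question "Was it relevant to alert you". Time without an alert is not rated. The same section says "The primary aim is to assess the sensitivity and specificity of the solution".

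The Discussion (Strengths and Limitations) expects the learning algorithm to increase "performance over time based on the end user feedback".

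Two other elements bear on the point. Statistical Analysis says the number and frequency of alerts will be recorded. It also says: "For the secondary objective, we will also analyze these 3 periods to evaluate the performance of the automatic alerts", using sensitivity, specificity, predictive values and ROC curves against functional or cognitive change or major events.

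**The concern.** PPV answers one question: of the alerts sent, what share did users find relevant? Progression of a monitoring system also involves how much relevant information users receive. Because ratings exist only where an alert was issued, a relevant situation that passed without an alert never enters the data. Sensitivity and specificity against user-judged relevance, named as the primary aim in Study Measures, therefore cannot be computed from these ratings.

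The Discussion sentence on feedback gives this practical weight. The only per-alert user feedback described is the relevance rating, which is also the primary outcome. If the algorithm responds to it, dropping alerts of the kind users reject is a foreseeable way to raise PPV, and some useful alerts may go with them. At stake is the primary conclusion: performance could be described as having progressed while older adults and care partners receive fewer alerts they consider relevant.

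**Working it through.** **1. The plan's own figure.** Sample Size assumes 25 participants × 2 alerts = 50 alerts, half rated valid. The exact (Clopper-Pearson) 95% CI for 25/50, treating alerts as independent, is 35.5% to 64.5%, which matches the stated interval. That interval describes PPV over the whole follow-up and carries no information on the volume of relevant alerts by period.

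**2. When PPV rises.** Let R be relevant and N non-relevant alerts in a period. PPV = R/(R+N). From period 1 to period 2, PPV rises exactly when N2/N1 < R2/R1. The condition says nothing about whether R2 is below R1.

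**3. Illustration (hypothetical counts, not in the documents).**

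| | Relevant | Non-relevant | Total | PPV |
|---|---|---|---|---|
| Earlier period | 10 | 10 | 20 | 10/20 = 50% |
| Later period | 6 | 2 | 8 | 6/8 = 75% |

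N2/N1 = 2/10 = 0.20 and R2/R1 = 6/10 = 0.60, so PPV rises by 25 points. Relevant alerts delivered fall by (10 − 6)/10 = 40%.

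**4. Limits of the effect.** If both kinds of alert shrink equally, for example 10/10 to 2/2, PPV stays at 50%. With no alerts PPV is undefined. Only selective reduction raises it.

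**5. Do raw alert counts protect the reading?** Procedure says no automatic alert is generated in the first month.
- Months 0-2: 25 × 1 = 25 active participant-months. If the first five participants completed learning in their preliminary phase (an assumption), 20 × 1 + 5 × 2 = 30.
- Months 2-4 and 4-6: 25 × 2 = 50 each, ignoring dropout.

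An unchanged raw count from months 0-2 to 2-4 would conceal a fall in the monthly rate of 1 − 25/50 = 50%, or 1 − 30/50 = 40%. Raw counts are also not split by relevance.

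**6. Does the secondary analysis protect it?** Its reference is medical events and autonomy change, which the Discussion says the primary endpoint is meant to go beyond. Major events are collected every 2 months, but function and cognition are assessed only at baseline and 6 months, so they give no reference for a single 2-month period.

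**7. What the proposed rates would show.** Place the illustration in months 2-4 and 4-6, with 50 active participant-months each. The relevant rate goes from 10/50 = 0.20 (exact Poisson 95% CI 0.10 to 0.37) to 6/50 = 0.12 (0.04 to 0.26) per participant-month. The non-relevant rate goes from 10/50 = 0.20 to 2/50 = 0.04. The reader now sees that both fell.

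**8. Precision by period.** Assume the 50 alerts are spread evenly and are all automatic: 50/3 ≈ 17 per period. The exact CI for 8/17 is about 23% to 72%. Power to detect a PPV change from 50% to 75% between two such periods is about 32% (two-sided 5%, normal approximation, independent alerts). Both PPV and the rates will be imprecise.

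**The case against.** A reader might infer that a system that simply goes quiet would be reported as improving, or that a rising PPV is built in because the algorithm is tuned on the outcome. The documents support neither. Uniform silencing leaves PPV unchanged and complete silence leaves it undefined. The feedback link rests on one Discussion sentence phrased as an expectation. The Methods describe learning from a month of sensor data and refer elsewhere for the algorithm, so how ratings enter, if they do, is unknown. Later alerts would also receive fresh ratings, so a higher PPV is not guaranteed.

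Second, dropping non-relevant alerts is partly what users want: the Discussion names false positive alarms as a main obstacle to acceptability. Alert numbers are recorded, and any PPV with a CI needs a numerator and a denominator, so a fall in volume could be seen. This stands in part. The counts will exist, but the plan does not tie them to the reading of progression, split them by relevance or relate them to active alerting time.

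Third, the illustration is invented and small. Exact CIs are about 27% to 73% for 10/20 and 35% to 97% for 6/8, they overlap widely, and the plan sets no success threshold. That is fair: the example shows direction, not a forecast.

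Fourth, the relevant-alert rate depends on how many relevant situations occur as well as on detection. A quiet period could lower it with detection unchanged. This stands, and it rules out a pass/fail criterion built on these rates.

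**Conclusion.** The point holds for the primary, user-rated analysis. Period PPV is its only stated measure of progression, and it can rise while relevant alerts delivered fall: by 25 points with 40% fewer relevant alerts in the illustration. This follows from the definition of PPV and from ratings being gathered only after alerts. It needs no assumption about how the algorithm learns; the Discussion sentence on feedback only makes selective reduction plausible.

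It would go too far to say that progression is assessed by PPV alone in the whole study, since the secondary analysis covers the same periods with other measures. Those measures use a different reference and do not replace the missing information. The frequency of the problem cannot be estimated from the documents. The 40% to 50% distortion of raw counts rests on full follow-up and on when the first five participants completed learning.

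**What to change.** In Statistical Analysis, beside the PPV for each 2-month period, report with 95% CIs:
- relevant automatic alerts per participant-month of active automatic alerting;
- non-relevant automatic alerts per participant-month of active automatic alerting.

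Active time excludes the learning month. Add one sentence: a rise in PPV accompanied by a lower relevant-alert rate will not by itself be interpreted as improved performance.

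Do not add a pass/fail rule, and do not label such a result as suppression. The relevant-alert rate also reflects how many relevant situations occurred, and missed situations are not measured.

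The cost is analysis wording only, because alerts and ratings are already collected. The period rates will be imprecise at about 17 alerts per period, and a claim of progression becomes somewhat harder to make.

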### Setting and Participants

All participants must give their written informed consent to take part in the study. Ethical approval was obtained from the Regional Independent Ethics Committee in June 2017 (ID-RCB: 2017-A01002-51).

This solution targets older adults, living with or at risk of functional or cognitive disability and living alone. The detailed inclusion criteria are as follows: aged 75 years or above, living alone at home; frail according to Fried criteria [12] or living with a disability but with an ADL score [13] 3 out of 6 or above; able to walk without help; and provision of written informed consent.

The exclusion criteria are as follows: patient presenting a Mini Mental State Examination (MMSE) <16 out of 30 and without daily care partner support; and under curatorship or guardianship.

Study participants are enrolled through a prescreening procedure on the basis of public administrative records held by several town halls in the region (person aged 75 years or above, living alone at home, and able to walk without help). A clinical research assistant (CRA) then conducts a preinclusion visit by phone. The inclusion visit with the principal investigator (AP) takes place in the Geriatrics Unit at the Toulouse University Hospital.

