### Follow-Up Procedure

The first 5 participants are enrolled for a total of 10 months (an initial 4-month period followed by a 6-month follow-up period) and the other 20 participants for 6 months. An installation visit will take place in the days following enrollment. A remote follow-up evaluation will be carried out over the phone by a CRA every 2 months after the baseline assessment (see Table 2). The last visit will be conducted by the CRA in the participant’s home after 6 months. For the first 5 participants enrolled in the study, the baseline for data analysis is defined as the beginning of the 6-month follow-up period at the end of the first preliminary 4-month period which is dedicated to technical feasibility. The proper regulatory and ethical conduct of the study is monitored by a clinical research technician, acting on behalf of the University Hospital.

**Table 2 table2:** Data collection.

Variables	Preinclusion (CRA^a^, in-person)	Baseline T0 (investigator)	T2 months (CRA, phone)	T4 months (CRA, phone)	T6 months (CRA, in-home visit)
Informed consent	✓	✓	—^b^	—	—
Sociodemographic data	—	✓	—	—	—
ADL^c^, IADL^d^, MMSE^e^	—	✓	—	—	✓
Frailty criteria, SPPB^f^	—	✓	—	—	✓
Acceptability questionnaire, EQ5D^g^	—	✓	✓	✓	✓
Major medical events	—	✓	✓	✓	✓
Sensor data	—	Continuous measures	Continuous measures	Continuous measures	Continuous measures

^a^CRA: clinical research assistant.

^b^Data not collected.

^c^ADL: activities of daily living.

^d^IADL: instrumental activities of daily living.

^e^MMSE: mini mental state evaluation.

^f^SPPB: short physical performance battery.

^g^EQ5D-3L: EuroQol 5D score to describe and value health, quality of life questionnaire.

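### Detection of functional and cognitive decline is planned by 2-month period, but decline is measured only between T0 and T6, so no period has its own reference outcome

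*Protocol article*

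**What the plan says.** The Statistical Analysis section first defines the periods for the primary PPV analysis: "each 2-month follow-up period: 0-2 months, 2-4 months, and 4-6 months". It then reuses them for the secondary aim: "we will also analyze these 3 periods to evaluate the performance of the automatic alerts in detecting changes in functional or cognitive autonomy". The same sentence names major medical events as a second target. The performance measures are sensitivity, specificity, predictive values and ROC curves. Alerts enter in two ways: as none versus one, and as a count over the period.

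On the reference outcome, Study Measures says of the participants that their "cognitive and functional parameters are assessed at baseline and at the end of follow-up". Table 2 under Follow-Up Procedure agrees. The rows "ADL^c^, IADL^d^, MMSE^e" and "Frailty criteria, SPPB^f" are ticked at T0 and T6, and T2 and T4 carry the dash that the footnote defines as data not collected. Major medical events, in the same table, are ticked at T0, T2, T4 and T6.

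The Procedure section adds that the first month serves algorithm learning, with no automatic alerts generated.

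**The concern.** Sensitivity and specificity for a period need two things from that period: the alert record and the true state. The alert record exists for all three periods. For functional and cognitive autonomy the true state does not, because change needs a measurement at both ends of the interval. The article states the schedule twice, consistently, and then states an analysis that the schedule cannot supply. This is not a detail left out by condensation, and a separate analysis plan could not create assessments at T2 and T4.

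Detecting functional and cognitive decline is half of the secondary objective. The Discussion says these results are meant to help size a future study. If period tables were produced by setting three alert windows against one 6-month outcome and labelled as detection by period, the mismatch would pass into that planning.

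**Working it through.** **Plan's own figure.** The article gives no number for the decline analysis. Its only worked planning figure is the interval in Sample Size: 25 participants × 2 alerts = 50 alerts, half rated valid. The exact (Clopper-Pearson) 95% CI for 25/50 is 35.53% to 64.47%, which reproduces the stated 35.5% to 64.5%. That figure belongs to the primary PPV, and nothing below depends on it.

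**Schedule against periods.** Rule: a period has a decline outcome only if the battery is given at both its start and its end. Visits are taken from Table 2.

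| Interval (months) | Decline battery at start | Decline battery at end | Decline outcome? | Major events covered? |
|---|---|---|---|---|
| 0-2 | yes (T0) | no (T2) | no | yes |
| 2-4 | no (T2) | no (T4) | no | yes |
| 4-6 | no (T4) | yes (T6) | no | yes |
| 0-6 | yes (T0) | yes (T6) | yes | yes |

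So 0 of 3 periods have a decline outcome, and each participant yields one change score, T0 to T6. For major events, 3 of 3 periods are covered.

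**What the remaining computable version would measure.** One can still tabulate each period's alerts against the T0-T6 change. Two features follow.

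1. The outcome column is identical in all three tables, because each participant carries the same decline status throughout. The tables can differ only through the alerts.
2. The decline is undated. An alert in 0-2 months may precede it by months, and an alert in 4-6 months may follow it. Neither can be classed as detection in that period.

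**Unequal alert-live time.** For the 20 regular participants, with month 1 silent:

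- 0-2 months: 2 − 1 = 1 live month each, 20 × 1 = 20 person-months
- 2-4 months: 2 live months each, 20 × 2 = 40 person-months
- 4-6 months: 2 live months each, 20 × 2 = 40 person-months

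This assumes no dropout and installation at baseline; installation some days later shifts the figures slightly. The first 5 participants start the analysed 6 months after a 4-month preliminary phase. The article does not say whether a learning month is repeated for them. If it is not, they add 5 × 2 = 10 person-months to each period, giving totals of 30, 50 and 50. If it is, they add 5, 10 and 10, giving 25, 50 and 50. Either way the first period has 50% to 60% of the alert exposure of the later ones. With the same outcome in every table, a lower sensitivity and higher specificity in 0-2 months could arise from exposure alone.

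**The case against.** The strongest reply is that the analysis can be run. The plan counts alerts over the period, and Conclusions and Perspectives speaks of retrospective correlations, so relating each period's alerts to the 6-month change is a possible reading. Since the Background aims at early detection of subtle change, an alert that comes well before a decline seen at T6 need not be wrong. This stands in part. A reader might infer that period-specific results cannot exist at all, and that goes too far. But the article does not state this reading, and what it would estimate is the association of early, middle or late alerts with a 6-month outcome, not detection within each period.

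Second, the sentence also covers major events, which are collected every 2 months. That stands fully, and the point is limited to decline.

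Third, EQ-5D is collected at T2 and T4. The article describes it as a general health measure and nowhere makes it the reference for functional or cognitive change.

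Fourth, the Discussion already concedes that follow-up is probably too short for loss of autonomy. That concerns how many declines will occur, not when they are measured. It limits the consequence but does not remove the mismatch.

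**Conclusion.** The point holds for the decline half of the secondary analysis. It rests on the visit schedule alone: 0 of 3 periods have their own decline outcome, while the 0-6 month interval does. The unequal exposure for the 20 regular participants (about 1, 2 and 2 live months) follows from the silent first month. The three-period analysis of major events, the primary PPV analysis and the precision example are untouched. It should be fixed, as a matter of the secondary objective.

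Three stronger readings are not supported:

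- **That the any-alert rule would be positive for nearly everyone over 6 months.** The 2 alerts per participant in Sample Size are an illustration and are not stated to be automatic alerts. The spread of counts between participants is not given.
- **That the plan would report a false improvement in decline detection over time.** Statistical Analysis ties progression of performance to the user-rated PPV and states no such aim for decline.
- **That a change of assessor and setting would masquerade as decline.** The inclusion visit "takes place in the Geriatrics Unit at the Toulouse University Hospital", Table 2 gives T0 to the investigator, and "The last visit will be conducted by the CRA in the participant’s home after 6 months". The change is real, but the documents give neither its size nor its direction. Having the CRA take over the T0 tests at the hospital visit would leave the setting difference, and doing so only for later participants would mix baselines, since the first 5 have already completed their first phase.

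**What to change.** Reconcile Statistical Analysis with Study Measures and Table 2:

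1. Keep the 0-2, 2-4 and 4-6 month analysis for major medical events only.
2. Analyse functional and cognitive decline once, T0 to T6, against automatic alerts over the whole alert-live time, by ROC curve and AUC. Use the count where live time is equal across participants and the rate where it is not, as may be so between the first 5 and the other 20.
3. Report any binary alert result for decline over that same window.

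The cost is wording in one section, with no added visit or measurement. What is lost is the set of period-specific decline tables, which could not have been validly produced. If the investigators do want each period's alerts related to the T0-T6 change, they should say so explicitly and describe it as an association with a 6-month outcome under unequal alert exposure.

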**Figure 2 figure2:**
[figure not shown]
Presentation of the overall solution. In this configuration, the solution comprises 4 passive infrared sensors to monitor activity (bedroom, kitchen, living room, and entrance hall); 1 contact sensor on the main entrance door; 1 cookie sensor on the fridge to monitor door opening; a pendant (or wristband) with a push-button emergency alarm; and a live intercom system (device in the left of the illustration) for direct audio communication with the support center (calling function).

The following data will be monitored: presence (yes/no) in specific rooms, for example, rooms associated with eating, bathing, and sleeping; time spent outdoors; total activity inside the home (estimated by the average number of sensor activations per day) [6]; fridge use; and sleeping patterns.

The solution can trigger 2 different types of alerts. The first consists of *conventional alerts*. They are generated by the participants using an alarm push button or through the intercom system. The second type of alert assessed in this project is automatically triggered by our artificial intelligence algorithm after an initial learning phase (eg, gradual change in sleeping pattern). The sensor-based alerts and the use of the Live intercom calling function are both directed to a telecare worker on a nationwide telecare platform (IMA/Serena) all 7 days a week and 24 hours a day. The telecare worker can suggest a range of actions, from direct contact with the older individual to a phone call to the care partner or to emergency services. The first month is dedicated to algorithm learning: all sensors are functional, but no automatic alert is generated from the platform. Activity data relating to sleeping, eating, and time spent outdoors, and so on, are recorded and analyzed. After the first month, there will be sufficient data to detect unusual behaviors and eventfully trigger an alert. The algorithm used to perform real-time detection of behavioral anomalies is described elsewhere [14].

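### Secondary analysis of major events: with no time order inside a 2-month period, and emergency calls counting as events, some alerts are credited as detections when they detected nothing

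*Protocol article*

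**What the plan says.** All references are to the protocol article.

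- **Statistical Analysis, unit:** the secondary aim is analysed by period: "we will also analyze these 3 periods to evaluate the performance of the automatic alerts in detecting changes in functional or cognitive autonomy or major" (that is, major medical events, the subject of this point).
- **Statistical Analysis, index test:** alerts enter in two forms. One is a "binary approach (no alert vs 1 alert to estimate sensibility, specificity, PPV, and negative predictive value"; the other is the "number of alerts over the period to plot an ROC graph and estimate the area-under-the-curve". Neither form says when in the period the alert must fall relative to the event.
- **Study Measures, reference standard:** a major medical event is "any event resulting in in-home physician or paramedic intervention, or a call to the emergency services". These events "are collected retrospectively by the CRA every 2 months (by phone".
- **Procedure (text after Figure 2), route of an alert:** "The sensor-based alerts and the use of the Live intercom calling function are both directed to a telecare worker". That worker's possible actions run from contacting the older person "to a phone call to the care partner or to emergency services".
- **Procedure, learning phase:** the sensors run during the first month, but the platform issues no automatic alert.

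**The concern.** Specificity and negative predictive value need units without an alert, so the natural unit of the stated analysis is one participant in one 2-month period. Two things follow from the text.

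1. **No time order.** If an event and an alert fall in the same period, the period is a true positive. That holds even if the alert came weeks after the event was dealt with, or was triggered by the inactivity of an empty home during a hospital stay. The count-based ROC curve has the same weakness, since alerts provoked by an event raise the count in event periods.

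2. **The index test can produce the reference standard.** The event definition rests on the response (a visit or a call), not on a confirmed medical problem. An automatic alert that the telecare worker escalates to the emergency services can therefore supply the event that confirms it. The article states no exclusion or separate adjudication of such calls.

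Detection of major events is a stated secondary objective. The Discussion (Strengths and Limitations) intends these performance figures to help size a future study, so favourable accuracy could carry over into that design.

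**Working it through.** **The plan's own figure.** The only numerical example is in Sample Size: 25 participants with 2 alerts each, half rated valid, is 25 of 50. The exact (Clopper-Pearson) 95% interval is 35.5% to 64.5%, which matches. That figure concerns the user-rated primary PPV. The article gives no figure for major-event accuracy, so what follows is an illustration.

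**Inputs**
- From the article: 2 alerts per participant in 6 months, so λ = 2/3 = 0.667 per 2-month period. This is the article's example, not an observed rate, and it may include conventional alerts.
- Assumed: alerts are Poisson and unrelated to health. Genuine events occur at μ = 0.1 or 0.2 per period. r is the chance that an event provokes an alert after it has been managed. q is the chance that an alert leads to an emergency call that counts as an event.

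**Baseline (q = 0, r = 0)**
- Sensitivity = 1 − exp(−0.667) = 0.487.
- Specificity = exp(−0.667) = 0.513.
- AUC at the any-alert threshold = (0.487 + 0.513)/2 = 0.50.
- PPV equals the event prevalence, 1 − exp(−μ) = 0.095 or 0.181.

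Matching within a period therefore gives uninformative alerts no credit by itself. The two mechanisms have to be added to see an effect.

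**Mechanism 1 alone (r = 0.3)**
- Sensitivity = 1 − 0.513 × 0.7 = 0.641; specificity stays at 0.513.
- AUC at that threshold = (0.641 + 0.513)/2 = 0.577.
- PPV for μ = 0.1: 0.641 × 0.095 / (0.641 × 0.095 + 0.487 × 0.905) = 0.122, against 0.095. For μ = 0.2 it is 0.226, against 0.181.

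**Mechanism 2 alone (q = 0.1)**
- P(an alert creates an event) = 1 − exp(−0.0667) = 0.0645.
- For μ = 0.1, P(event) = 1 − 0.9048 × 0.9355 = 0.1535 and P(event with no alert) = 0.0952 × 0.5134 = 0.0489.
- Sensitivity = 1 − 0.0489/0.1535 = 0.68; specificity = 0.5134/0.9355 = 0.549; PPV = (0.1535 − 0.0489)/0.4866 = 0.215.
- For μ = 0.2, sensitivity is 0.60 and PPV 0.29.

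**Summary for alerts that carry no information**

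| q | r | Sensitivity | Specificity | PPV |
|---|---|---|---|---|
| 0 | 0 | 0.49 | 0.51 | 0.10–0.18 |
| 0 | 0.3 | 0.64 | 0.51 | 0.12–0.23 |
| 0.1 | 0 | 0.60–0.68 | 0.55 | 0.22–0.29 |
| 0.1 | 0.3 | 0.72–0.78 | 0.55 | 0.24–0.33 |

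Ranges cover μ = 0.1 and 0.2. A simulation under the same assumptions agrees with these values.

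**Forces in the other direction.** Alerts are silent for 30 of the first 60 days. With events spread evenly, a perfect real-time detector would reach only about 50% sensitivity in months 0–2 and 5/6 = 83% over 6 months. This applies at least to the 20 participants without the 4-month preliminary phase. An alert whose response averts an event is scored as a false positive.

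**The case against.** - **Alerts after onset are often what the system is for.** The Background gives hours without movement after a night-time visit to the bathroom as an example of what should trigger an alert. This stands. A rule that credits only alerts before onset would give a perfect fall detector zero sensitivity for falls. The criticism applies only to alerts after the event was recognised or managed.
- **A reader might take the 49% sensitivity of unrelated alerts as proof of inflation.** It is not. It comes with 51% specificity, an AUC of 0.5 and a PPV equal to prevalence, and the plan reports these measures together.
- **A reader might infer that nearly half of the detections would be spurious.** With uniform event times, the chance of at least one earlier alert is 1 − 0.487/0.667 = 0.270, so 1 − 0.270/0.487 = about 45% of chance detections have none. But this treats every alert after onset as invalid, so it does not measure error.
- **An escalated false alarm may not be an event at all**, because the definition requires something that resulted in an intervention or call. The wording can be read that way. It requires no confirmed problem, however, so the point is left open. Study Measures already records the solutions proposed after each alert, which should help to identify such calls.
- **An article may leave matching rules to the full protocol or SAP.** They may indeed be there. The article nonetheless states a period-level rule, and followed as written it has these effects.
- **The consequence is limited.** The Conclusions call these analyses retrospective correlations that need prospective confirmation, and the Discussion says other studies at the centre can support sizing. Both lower the stakes, but neither addresses the two mechanisms.

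**Conclusion.** The concern holds in a limited form. As written, the secondary analysis credits alerts raised after an event was already known or managed, or during absence from home, and it lets an alert-triggered emergency call serve as its own confirmation. Each mechanism pushes sensitivity, PPV and AUC for major events upward.

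The size is unknown. The illustrated rise in sensitivity, from 0.49 to between 0.60 and 0.78, rests on assumed values of q, r and the event rate, and on the article's example alert rate.

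A reader might conclude that the reported accuracy will be too high overall. The document does not support that: the silent first month and averted events work the other way, so the net bias is uncertain, especially in months 0–2. Nor does the point touch the primary outcome, the PPV rated by users.

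**What to change.** 1. At the existing 2-monthly call by the clinical research assistant, record for each major event its date (including when it was recognised or help arrived), who placed any call, and whether a medical problem was found.
2. Count an event as detected only if an automatic alert fell in a prespecified window that ends when the event was recognised or help arrived. Alerts after onset but before recognition still count.
3. Exclude alerts after recognition and alerts during known absence from home. Use event-free windows of the same length for specificity.
4. Report accuracy with and without events whose only qualifying feature is an emergency call placed by the platform in response to an automatic alert, with no medical problem found.

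The cost is two or three extra data fields and slightly more analysis. The accuracy figures will probably be lower.
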